#### Baseline assessment and covariates

Demographic variables (age, sex, care level, and highest educational level), main medical diseases, and medications will be obtained from medical records by trained study assistants. Data regarding skin self-care ability, incontinence and type will be obtained from the medical records or, if possible, via interview of the nursing home residents or the caregivers.

Functional assessments using the Braden scale and Barthel - Index will be conducted. The Braden scale is a six-item pressure ulcer risk assessment score with scores ranging from 6 (high-pressure ulcer risk) to 23 (no-pressure ulcer risk). The Barthel - Index measures physical function related to the daily activities using 10 items (e.g., washing and toilet use, eating and mobility or incontinence). Scores range from 0 (very dependent) to 100 (not dependent) [39].

All residents will be interviewed regarding their skin care habits. Data will be documented in structured source documents by trained study assistants. Variables for assessing skin care routine will be (1) washing habits, (2) showering habits, (3) bathing habits, (4) moisturizing habits of the face and body, (5) hair care, and (6) shaving habits. For all variables, the frequency, skin areas, used skin care products, and the residents’ ability to apply skin care by themselves will be documented. In case of cognitive impairment of the resident, the respective nurse will be asked or the information will be obtained from the medical records.

The residents or their caregivers will be asked regarding the date of the last visit by physician/specialty in week 0. If possible, the following information will obtained from the medical records:Is there a documentation of pressure ulcer risk in place?Are skin assessment results documented?If applicable, the type of pressure ulcer preventive mattress or seating cushion;The repositioning interval if bedfast;Seating hours if not able to stand up independently;Off-loading of heels if exposed to high risk of pressure ulcer;Skin care interventions provided (cleansing and leave-on products);Use of incontinence products and types;Incontinence skin care products.

To assess the degree of implementation of the skin care package and possible moderating or mediating effects of context factors, further quantitative and qualitative data will be gathered at resident, staff, and institutional levels for process evaluation [40]. The protocol of this mixed methods study embedded in the trial will be reported separately elsewhere.

### Randomization and recruitment

A 1:1 simple random generation of the allocation sequence of nursing homes to intervention (*n* = 10) or control group (*n* = 10) will be undertaken by an independent data manager via a computer-generated random list. The allocation will be conducted by the investigator using numbered opaque envelopes (1 to 20) containing computer-generated random numbers.

Nursing homes will be randomly selected from a comprehensive list of all nursing homes in Berlin (*n* = 288). Potentially eligible nursing homes will be contacted and invited to participate by letter. If there is no response by a defined deadline, the next randomly selected nursing home will be invited. If applicable, baseline characteristics (e.g., number of beds) of non-responders and reasons for non-participation will be listed in order to estimate a possible selection bias. In the case of small institutions with fewer than 70 beds/residents, the next randomly selected institution will be invited.

Recruitment of the nursing home residents and baseline measurements will be completed prior to random allocation of the nursing homes. Posters and flyers will be placed in public areas in the nursing homes to inform residents and relatives as a first step. The recruitment onsite the nursing homes will be carried out in close cooperation with a nominated key project leader of the participating nursing home. The key project leader will inform possible residents and hand out information leaflets or letters. Interested residents or their legal representatives will be contacted by the study team personally and will be invited to participate in the study.

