## Trial status

This trial is registered at the German Clinical Trials Register and ClincialTrials.gov. The local ethics committee (EA1/243/18) approved the study on January 11, 2019. At the time of submission of this manuscript, the recruitment of the nursing homes had been started. The first 12 nursing homes expressed interest. Of them, six nursing homes committed to participation and were in preparation to start the study in April and June 2019. Six other nursing homes have confirmed appointments for the first information meetings.

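### The article calls the allocation simple 1:1 randomisation but fixes 10 homes per arm; if 10/10 is enforced in sequence, the last one or two allocations can be deduced before their residents are recruited

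*Protocol article*

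**What the plan says.** All main statements are in the protocol article, section Randomization and recruitment.

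- **Method:** "A 1:1 simple random generation of the allocation sequence of nursing homes to intervention". No block or other restriction is named.
- **Arm sizes, in the same sentence:** "nursing homes to intervention (*n* = 10) or control group (*n* = 10". The section Sample size calculation also uses 10 homes per arm.
- **List generation:** it "will be undertaken by an independent data manager via a computer-generated random list".
- **Allocation:** "The allocation will be conducted by the investigator using numbered opaque envelopes (1 to 20) containing computer-generated random numbers". The order and timing of opening are not given.
- **Safeguard:** "Recruitment of the nursing home residents and baseline measurements will be completed prior to random allocation of the nursing homes". The article does not say whether this applies home by home or to all 20 homes together.
- **Approach to residents:** the home's key project leader informs residents, and then "Interested residents or their legal representatives will be contacted by the study team personally" and invited to take part.

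The section Blinding covers the dermatological outcome assessors, the data manager and the trial statistician. It does not mention those who recruit residents. The section Trial status says that the first six homes "were in preparation to start the study in April and June 2019", while six others still had only appointments for a first information meeting.

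**The concern.** Simple randomisation, in the usual sense of an independent 1:1 draw for each home, does not guarantee 10 and 10. A list that does guarantee it is restricted: in effect one block of 20. The article states both, and they have different properties. An unrestricted list cannot be predicted but may leave the arms unequal. A fixed 10/10 list keeps the arms equal, but anyone who knows the earlier allocations can work out its end.

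This matters because the protection against selective recruitment is that residents are enrolled before their home is allocated. That works only while the coming allocation cannot be foreseen. There is room for selection: about 25% of residents are expected to take part, and they are approached individually. The analysis population is defined as residents who have passed the baseline visit, so an intention-to-treat analysis cannot undo selection that happened before allocation.

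**Working it through.** **1. The plan's own power figure.** Inputs from Sample size calculation: 10 homes per arm, 23 residents per home, ICC 0.02, 29.3% versus 16.2% at six months, two-sided 0.05.
- Design effect = 1 + (23 − 1) × 0.02 = 1.44.
- Effective number per arm = 230 / 1.44 = 159.7.
- Power of the two-proportion Z-test = 80.0% (pooled variance) or 80.7% (unpooled).

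The stated figure is reproduced, and it rests on exactly 10 homes per arm.

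**2. Does simple randomisation give 10/10?** With the number of intervention homes X ~ Bin(20, 0.5):
- P(10/10) = C(20,10) / 2^20 = 184,756 / 1,048,576 = 17.6%.
- P(8/12 or more uneven) = 50.3%.
- P(7/13 or more uneven) = 26.3%.

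**3. Does the calendar allow one draw for all 20 homes?** Inclusion starts in April 2019, the last resident completes in March 2021, and follow-up is 24 ± 1 weeks.
- Last inclusion: March 2021 minus 23 to 25 weeks, so 7 September to 21 October 2020.
- First homes' follow-up ends about mid-September to late October 2019.
- Gap between first and last inclusion: about 71 to 81 weeks.

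The first homes would finish follow-up about a year before a single draw after all recruitment could take place. Allocation must therefore be staggered, singly or in batches.

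**4. What can be deduced from a fixed 10/10 list opened one home at a time?** All 184,756 sequences are equally likely. A home is known in advance when it and every later home fall in the same arm, so P(last L homes known) = 2 × C(20 − L, 10 − L) / C(20,10).

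| Last L homes known | Probability |
|---|---|
| 1 | 100% |
| 2 | 47.4% |
| 3 | 2 × 19,448 / 184,756 = 21.1% |
| 4 | 2 × 8,008 / 184,756 = 8.7% |

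Mean number known = 2n/(n + 1) = 20/11 = 1.82 homes. At 25 residents per home that is about 45 of 500.

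Short of certainty, the best guess is right with these probabilities:
- Homes 16 and 17: 66.7%.
- Home 18: 0.211 × 1 + 0.789 × 2/3 = 73.7%.
- Home 19: 0.474 × 1 + 0.526 × 1/2 = 73.7%.

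Over the whole list, 12.3 of 20 guesses are right, against 10 by chance.

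**5. Effect of a final batch.** If the last three homes are drawn together after all their residents are enrolled, the batch is known beforehand only when all three share an arm: 21.1%. For four homes it is 8.7%. Compare this with home 20 always being known. Batching limits certainty but does not abolish guessing: a best guess for each home in a batch of three is still right 73.7% of the time.

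**The case against.** **The wording may be loose.** *Simple* may mean unstratified, with 10 of 20 homes drawn at random. Envelopes numbered 1 to 20, the 10 and 10 in the same sentence and the power calculation all favour that reading. This stands, and it is why the remedy is to name the restriction rather than to change the arm sizes.

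**Home-by-home opening is not written.** A reader might infer that the investigator is to open envelopes one home at a time. The article does not say so, and starts in April and June 2019 also fit batches. The calendar excludes only a single draw after all homes have recruited.

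**Two harms must not be added together.** A reader might infer both that power is lost through unequal arms and that allocations are predictable. These belong to different readings. Under truly simple randomisation nothing can be deduced. Binary power would then be 75.1% to 77.4% at 7/13 and 77.8% on average over all splits, against 80.0%. Under a fixed 10/10 list the arms are equal and power is unaffected. The stated power itself was reproduced, so this point shows no loss of power under the fixed list.

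**The route to bias is partly closed.** The home's own project leader makes the first approach to residents, and nothing says that this person knows other homes' allocations. A separate blinded group makes the dermatological assessments. What remains open is the study team's personal contact and invitation: the article does not say that this team knows earlier allocations, but nothing in it keeps them hidden.

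**A condensed article.** Custody of envelopes and release triggers may be in the full protocol, and their absence here is not criticised. The mismatch between the named method and the fixed arm sizes is in the printed text.

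**Conclusion.** The point holds in two parts. First, without qualification: the named method and the fixed arm sizes do not agree, since simple randomisation would give the planned 10/10 in only 17.6% of cases. The text should be corrected.

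Second, conditionally: if 10/10 is enforced, homes are allocated one after another, and those who invite residents can learn the earlier allocations, then the last one or two homes are open to deduction. Home 20 is always known and the mean is 1.8 homes, or about 9% of planned residents (45/500). The first two conditions are the likelier reading of the text and calendar; the third is neither stated nor excluded. Recruiting before a home's own draw does not remove the problem, because the running tally comes from the other homes.

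The likely bias is small, and the trial is exploratory with unadjusted p values. Its results and ICCs are nevertheless meant to support a confirmatory trial, and the correction is cheap enough to be worth making.

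**What to change.** For homes not yet allocated:

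1. Replace the simple 1:1 wording with a statement of restricted randomisation of 20 homes to 10 and 10. For homes already allocated, report how the list was in fact made.
2. Allocate the remaining homes in batches, and in particular the final three or four together, only after all their residents are enrolled and baseline is complete in every home of the batch.
3. Have allocations released by an independent person. This should not be the data manager whom the Blinding section describes as blinded; the article does not say whether that is the same person who generates the list. A change of custody alone would not be enough, because the tally can still be counted once homes start their arms.
4. Keep those who recruit residents unaware of the tally, and add this to the Blinding section.

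The cost is a short wait for homes in the final batch, a little administration and a wording change. Sample size and analysis stay as they are.

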### Blinding

One group of investigators and study nurses administers the interventions and communicates with participating nursing homes. A second independent group of outcome assessors (including dermatologists/residents of dermatology) will complete the dermatological assessments while blinded to the allocation. The data manager and trial statistician will be blinded during data management and statistical analysis.

### Sample size calculation

Because the trial is exploratory in nature, a primary outcome is not defined. The sample size is determined such that the power of statistical tests is sufficiently high for each of several binary and continuous outcomes under realistic assumptions. According to the federal state government, there are 288 nursing homes in Berlin. According to the latest statistics (2015), the total number of nursing home residents in Berlin is 28,299. Given a mean of 100 residents per institution and a participation rate of 25%, the expected total number of residents is 25 per participating institution (500 in total). Taking into account a drop - out rate of 8%, each participating nursing home contributes about 23 residents to the trial. If m = 10 nursing homes are included in each study arm and given an ICC of ρ = 0.02 [41] and an incidence for the skin conditions of around p_C_ = 50% per annum (p.a.) (29.3% in 6 months) in the control group, the two-sided Z-test for difference in proportions at a level of α = 0.05 has a power of more than 80% if in the experimental group skin condition worsens in less than p_E_ = 29.8% p.a. (16.2% in 6 months). The power calculation for the clustered binary outcome was carried out using the method described in Ahn et al. [42]. For metrical outcomes such as the ODS score, the two-sided t-test can detect a minimal effect size (Cohen’s d) of d = 0.33 with a power of 80% at a significance level of α = 0.05. Again, an ICC of ρ = 0.02 is assumed. Therefore, the detectable effect sizes are relatively small for all outcomes. Since the effects of the experimental skin care regimen are expected to be larger, the study is not underpowered for each variable.

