## Discussion

To the best of our knowledge, this is the first trial implementing a comprehensive evidence-based skin care and prevention strategy in institutional long-term care. The skin care and prevention strategy was developed systematically, taking currently available evidence and expert opinion into account. Given the novelty of this approach and its complexity, first an exploratory trial is needed in order to evaluate the feasibility of this intervention package and possible trial procedures and to gain insights into potential mechanisms of change and impacts on patient-important outcomes. Trial results will have impacts on clinical research and practice: In the short term, results will (1) prove the feasibility of the intervention package and provide robust data about relevant context factors and required implementation strategies to be considered for a confirmatory evaluation of the skin care program’s clinical effectiveness and cost-effectiveness and (2) inform the protocol for subsequent confirmatory trials (e.g., in regard to the responsiveness of outcome measures and associated effect sizes, ICCs, and data collection methods).

This trial will benefit individual patients and aged nursing home residents in general. According to the latest systematic reviews and researching [2, 3], the skin conditions of interest are frequent in this population: In German long-term and geriatric care facilities, the PU prevalence is approximately 4% [43–45], the prevalence of dry skin is approximately 53% [46] and associated pruritus up to 14% [46, 47], and the prevalence of IAD ranges from 4% to 11% [48, 49]. The incidence and severity of these skin conditions will be reduced; thus, patient safety will be enhanced. The improvement of dry skin helps to prevent secondary infection and pruritus. Overall, QoL will be increased. Potential unhelpful care interventions will be avoided. Carefully developed and targeted skin care practice will reduce patients’ exposure to unnecessary and inappropriate products, thus reducing the risk of irritation, contact allergies, and other adverse effects [11]. In addition, so far, often neglected and overlooked age-related skin conditions , especially symptomatic xerosis cutis, which is an explicitly stated unmet need of aged patients [50], will be addressed.

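### The claim of adequate power for each outcome rests on a single 50% yearly incidence and is unsupported for pressure ulcers, and for incontinence-associated dermatitis at its lower prevalence figure

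*Protocol article*

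**What the plan says.** The Sample size calculation section of the protocol article defines no primary outcome. It says the sample size was chosen so that "the power of statistical tests is sufficiently high for each of several binary and continuous outcomes under realistic assumptions". For binary outcomes it gives one calculation. The control arm has "an incidence for the skin conditions of around p_C_ = 50% per annum (p.a.) (29.3% in 6 months) in the control group", and power exceeds 80% if in the experimental arm "skin condition worsens in less than p_E_ = 29.8% p.a. (16.2% in 6 months"). The design inputs are 10 homes per arm, about 23 residents per home after drop-out, and an ICC of 0.02. The section then describes the detectable effects as fairly small for every outcome and closes: "Since the effects of the experimental skin care regimen are expected to be larger, the study is not underpowered for each variable".

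The Outcomes and measurements section names pressure ulcer (PU), incontinence-associated dermatitis (IAD), intertrigo and skin tear incidence as separate main outcomes, beside skin dryness. All outcomes are measured at weeks 0, 12 and 24. The Discussion reports that in German long-term and geriatric care "the PU prevalence is approximately 4" per cent and that "the prevalence of IAD ranges from 4% to 11" per cent. The article gives no incidence for any single condition.

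**The concern.** One incidence stands in for four different lesions, and the power statement is then extended to each of them. At a fixed risk ratio, the power of a test of proportions falls quickly as the control risk falls. A lesion present in about 4% of residents at a given time may well not arise in 29% of them within six months. If it does not, the trial lacks the stated power for it.

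PU is the first-named main outcome. A null PU result could be read as coming from a trial with more than 80% power when the data could exclude only a very large effect. The stated main aim is to provide a basis for a confirmatory trial, so the power claim should be accurate.

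**Working it through.** **Inputs** (Sample size calculation): 10 homes × 23 residents = 230 per arm; ICC 0.02; two-sided 5% Z-test; 29.3% against 16.2%. The risk ratio is 0.162/0.293 = 0.553.

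**1. The plan's own figure.**
- Annual to six-month risk: 1 − √(1 − 0.50) = 29.3%; 1 − √(1 − 0.298) = 16.2%. Both agree with the article.
- Design effect: 1 + 22 × 0.02 = 1.44. Effective n per arm: 230/1.44 = 159.7.
- Power = Φ(|p1 − p2| / √[(p1q1 + p2q2)/159.7] − 1.96) = Φ(0.131/0.0463 − 1.96) = Φ(0.87) ≈ 80.7%. The pooled-variance form gives 80.0%.

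The stated power is correct for its inputs, with almost no slack.

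**2. Same design and risk ratio, lower control risk.**

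| Control risk, 6 months | Experimental risk | Power |
|---|---|---|
| 29.3% | 16.2% | 81% |
| 20% | 11.1% | 60% |
| 15% | 8.3% | 47% |
| 11% | 6.1% | 35% |
| 8% | 4.4% | 26% |
| 4% | 2.2% | 15% |

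Adequate power for each binary outcome at this risk ratio would therefore require every condition to reach about 50% a year.

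**3. PU counted only at visits (no lesion duration needed).** Assume the Discussion's 4% holds in the control arm at each follow-up visit. Then at most 4% + 4% = 8% of residents can be seen with a PU at week 12 or week 24 (7.8% if the two visits were independent: 1 − 0.96²).
- Power at 8% and risk ratio 0.553: about 26%.
- Power at 8% and a 70% reduction (8% against 2.4%): about 62%.
- 80% power needs about 8% against 1.4%, a reduction of about 82%.

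**4. PU if all lesions between visits are captured.** Assume a steady state, with hazard h = P / [(1 − P) × D] for prevalence P and mean lesion duration D. The risk over follow-up of length T is 1 − exp(−hT). D is not in the article and is an assumption here. P = 4%, risk ratio 0.553:

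| Assumed D | Risk over follow-up | Power |
|---|---|---|
| 24 weeks | 4.1% | 15% |
| 12 weeks | 8.0% | 26% |
| 6 weeks | 15.4% | 47% |
| about 4 weeks (one month) | 20.6 to 22.1% | 62 to 65% |
| about 3 weeks (22 days) | 29.3% | 80% |

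In the one-month row the lower figures use 24 weeks of follow-up and the upper ones six months; the last row uses six months. Pooled and unpooled forms differ by less than one percentage point. The last row follows from the plan's own rate: 50% a year is a hazard of ln 2 = 0.693 per year, so D = (0.04/0.96)/0.693 = 0.060 years, or 3.1 weeks. With a 70% reduction instead, power is 36%, 62% and 90% at D = 24, 12 and 6 weeks.

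**5. IAD.** At 4% prevalence the figures are those for PU. At 11%, D = (0.11/0.89)/0.693 = 0.178 years, or 9.3 weeks. The upper IAD figure is therefore compatible with 50% a year if episodes average about 9 weeks and those between visits are captured.

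**6. Intertrigo and skin tears.** The article gives no rates, so nothing can be shown for them in either direction.

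**The case against.** The best defence is that no calculation is wrong, and that is so: the conversions and the binary power reproduce. A reader might infer an arithmetic error, but the fault lies in how far the conclusion is stretched.

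A reader might also infer that 4% prevalence proves a low incidence, or that PU power simply is 15 to 47%. The article does not support that. Prevalence fixes an incidence only through a lesion duration, which is not given. The 15 to 47% range belongs to assumed durations of 24 down to 6 weeks and a risk ratio of 0.553; about 3 weeks restores 80%. The 4% also describes German facilities in general and may not carry over to consenting residents aged 65 or over with care degree 2 or higher.

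The section also rests its conclusion on effects larger than the one calculated. That helps in part, since a 70% reduction reaches 90% power at a 6-week duration. It does not rescue the claim on the visit-count basis (62%) or at 24 weeks (36%). At a control risk of 4%, even zero events in the experimental arm gives only 73%.

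It would go too far to say that no outcome was sized. The continuous outcomes, including the dry skin score, have their own calculation. The 50% might also mean any lesion, or a worsening of a common condition such as dryness; the article does not say. On either of those readings the calculation still does not speak for PU.

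Finally, the trial is exploratory, has no primary outcome, and is meant to deliver effect sizes and ICCs. This limits the harm, because a later trial can be planned from observed rates. It does not make the sentence about each variable correct.

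**Conclusion.** The claim of adequate power for each variable is unsupported for PU, and for IAD at its lower prevalence figure of 4%. It is not shown to fail for IAD at 11%, for intertrigo, for skin tears or for the continuous outcomes.

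The firmest result is the dependence on control risk: at the plan's risk ratio, any condition below about 29% in six months falls short of 80%. The size for PU is conditional. It is about 26% if the 4% applies to this sample and only visit findings count, and otherwise anywhere from 15% to 80% as the assumed mean duration runs from 24 down to about 3 weeks. This is a correction to a stated power claim in an exploratory trial. It affects no estimate, no planned analysis and no resident number.

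**What to change.** In the Sample size calculation section:

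1. Withdraw the three blanket statements: sufficient power for each of several binary outcomes, small detectable effects for all outcomes, and no lack of power for each variable.
2. State which event the 50% a year refers to, and limit the 80% statement to binary outcomes with a six-month control risk of about 29% or more.
3. Give power or detectable differences over a range of lower control risks, for example 4 to 20%, labelled as assumptions and not as known rates. With the present design, 80% power corresponds to about 20% against 9.1%, 15% against 5.6%, and 8% against 1.4%. The last implies only about 230 × 0.014 ≈ 3 experimental-arm events, so the normal approximation is rough there.
4. Say that PU and low-rate IAD will be estimated with confidence intervals and are not tested with adequate power.

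An any-lesion outcome derived from data already collected is optional. The cost is rewording and a less favourable power statement for the rarer lesions; no extra residents or data are needed.

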### Nursing homes and participants

#### Eligibility criteria

The inclusion criteria at the institutional level are that (1) participating nursing homes must express a clear commitment to implement the skin care and prevention strategy if assigned to the intervention group, (2) participating nursing homes must have a valid PU prevention standard/algorithm in place, (3) only nursing homes providing written commitment to adherence to the trial procedures regardless of the outcome of randomization will be included, and (4) nursing homes have to have a minimum bed size of *n* = 70.

The inclusion criteria at the resident level are (1) living in the nursing home at the time of data collection, (2) age of at least 65 years, (3) “care degree 2 or higher” according to the German code book (Sozialgesetzbuch, or SGB) XI, and (4) written informed consent (from the resident or a legal representative). Residents at the end of life or with any dermatological condition or skin infestation requiring dermatological treatment or with known intolerance to any possible irritating product ingredients (e.g., urea or lactate buffer) or known hypersensitivity to any product ingredients (e.g., sorbid acid or cetylstearyl alcohol) will not be considered eligible.

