### Participant timeline

In total, four study visits are planned. After inclusion, residents will be followed up for 24 ± 1 weeks. Written informed consent will be obtained from the residents themselves or their legal representatives prior to study participation. All participating nursing home residents undergo a comprehensive demographic, nursing, medical, and dermatological examination. A detailed planned study schedule is shown in Fig. 1.

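### The binary power of more than 80% is optimistic: with 24-week risks and the 18 cluster degrees of freedom that the continuous figure appears to use, it is about 73%

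*Protocol article*

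**What the plan says.** The Sample size calculation section of the protocol article gives two power statements for the same design.

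- **Binary outcomes.** The control rate is "p_C_ = 50% per annum (p.a.) (29.3% in 6 months) in the control group" and the experimental rate is "p_E_ = 29.8% p.a. (16.2% in 6 months"). The design is introduced with "If m = 10 nursing homes are included in each study arm", an ICC of 0.02 and about 23 residents per home after 8% drop-out. The conclusion is that "the two-sided Z-test for difference in proportions at a level of α = 0.05 has a power of more than 80" percent.
- **Continuous outcomes.** With the same ICC, "the two-sided t-test can detect a minimal effect size" of d = 0.33 at 80% power.

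The section then concludes that no variable is underpowered.

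On duration, the Participant timeline section states: "After inclusion, residents will be followed up for 24 ± 1 weeks". The Outcomes and measurements section places the last visit at week 24 ± 1 and labels it 6 months. On home size, the Eligibility criteria section sets only a lower limit of 70 beds.

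**The concern.** The binary statement is a threshold at 80% power, so it has no reserve. Two of its ingredients are more favourable than the rest of the document allows.

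First, the 6-month risks are exact half-year conversions of the annual rates, while residents are observed for 24 weeks. Less exposure means fewer events and a smaller absolute difference.

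Second, the binary figure refers to a normal distribution, as if the between-home variation were known. The arms are compared across 20 homes, which leaves 2 × 10 − 2 = 18 degrees of freedom. The continuous figure in the same paragraph seems to allow for this, so the two figures are not on the same footing.

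At stake is how the results are read. The trial is meant to inform a confirmatory study. A non-significant binary result will be judged against the stated power, and a later trial may copy the method.

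**Working it through.** **Inputs (Sample size calculation).** 10 homes per arm, 23 residents per home, ICC 0.02, two-sided α = 0.05, annual rates 50% and 29.8%. Follow-up of 24 weeks comes from Participant timeline.

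**Effective sample size.** Design effect = 1 + (23 − 1) × 0.02 = 1.44. Effective n per arm = 230 / 1.44 = 159.7.

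**Step 1: reproduce the stated figure.**
- Risks: 1 − 0.50^0.5 = 0.2929 and 1 − 0.702^0.5 = 0.1621. These are the article's 29.3% and 16.2%, so the conversion covers exactly half a year under a constant hazard.
- Unpooled SE = √[(0.2929 × 0.7071 + 0.1621 × 0.8379) / 159.7] = 0.0463. The difference is 0.1307, and the ratio to the SE is 2.82.
- Power = Φ(2.82 − 1.96) = 80.6%. With a pooled variance it is 79.6%. (Entering the rounded risks 0.293 and 0.162 gives 80.7% and 79.7%.)

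**Step 2: 24-week risks, Z-test kept.** With a year of 52.18 weeks:
- 1 − 0.50^(24/52.18) = 0.2730 and 1 − 0.702^(24/52.18) = 0.1502.
- SE = √[(0.2730 × 0.7270 + 0.1502 × 0.8498) / 159.7] = 0.0452. The difference is 0.1228, and the ratio is 2.72.
- Power = Φ(2.72 − 1.96) = 77.6%. At the latest permitted visit, week 25, it is 79.1%.

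**Step 3: which basis does d = 0.33 use?** The detectable d at 80% power with 159.7 per arm is:
- normal approximation: (1.960 + 0.842) × √(2/159.7) = 0.313
- t on individual-level degrees of freedom: 0.314
- t on 18 cluster degrees of freedom: 0.332

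Only the last rounds to 0.33.

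**Step 4: apply 18 degrees of freedom to the binary figure.** The power comes from a noncentral t, with the ratios above as noncentrality and a critical value of 2.101.

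| Risks | Reference | Power, unpooled | Power, pooled |
|---|---|---|---|
| Half-year | Z | 80.6% | 79.6% |
| 24 weeks | Z | 77.6% | 76.6% |
| Half-year | t, 18 df | 76.1% | 75.0% |
| 24 weeks | t, 18 df | 72.9% | 72.0% |

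A 52-week year changes the last row to 73.1% and 72.1%. A beta-binomial simulation of a home-level t-test (40,000 runs, 24-week risks) gave 72.8%.

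**Step 5: move the threshold instead.** At 24 weeks on 18 degrees of freedom, 80% power needs an experimental risk of about 14.1%, or about 28.1% per annum. The like-for-like comparison is 14.1% with 15.0%, the 24-week risk that belongs to 29.8% per annum.

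**Sensitivity to unequal homes.** With the design effect 1 + [(1 + CV²) × 23 − 1] × 0.02 and both changes applied, power is 72.8% at CV 0.1 and 70.8% at CV 0.4. The article gives no CV, so this range is an assumption.

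**The case against.** The strongest reply is that the stated figure is correct for what it says it is. The article names its test, ICC and cluster numbers, and the result follows from them. That stands: a reader might infer an arithmetic slip, and there is none.

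A detectable-difference statement sits at 80% by construction, so any stricter assumption takes it below. That also stands. The movement of the threshold, from 29.8% to about 28.1% per annum, is the fairer measure of size. Setting 14.1% against the article's 16.2% would exaggerate it, because those risks cover different periods.

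The window effect is small against the uncertainty of its input. The article calls week 24 6 months and gives the control rate only as around 50% per annum. With the experimental half-year risk held at 16.2%, a control rate of 48% gives 72.0% power and 52% gives 87.4%. This limits the weight of the point, but the label does not turn 24 weeks of exposure into 26.

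The degrees of freedom behind d = 0.33 are not stated, and different formulas for binary and continuous outcomes are not in themselves a contradiction. The shared basis is therefore an inference, although 18 is the only one of the three candidates that fits.

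Two stronger readings are not supported:
- A reader might infer that the final tests will have an inflated type I error. The Statistical analysis section names generalized mixed-effects models without fixing a reference distribution, and that choice may be left to an analysis plan that is not shown.
- A reader might infer that unequal homes alone break the claim. With the Z-test and half-year risks, power is still 80.1% at CV 0.2 and drops under 80% only near CV 0.25 (79.8%). The minimum of 70 beds, about 17 residents at 25% participation, does not establish such a CV.

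**Conclusion.** The point holds as a moderate one. The statement of more than 80% power is reproducible but optimistic for the trial as scheduled, by about 3 points for the follow-up window alone, 4 to 5 for the degrees of freedom alone, and 8 for both. Either change alone takes the figure below 80%.

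The figure of about 73% rests on a constant hazard (which the article's own conversion also uses), equal homes of 23, an ICC of 0.02 and a t reference on 18 degrees of freedom. If only the window is accepted, the figure is about 77 to 78%.

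It is not a reason to hold up the trial. There is no primary outcome, all p values are exploratory, and no decision depends on 80% rather than 73%. What cannot stand unqualified is the conclusion that power is adequate for every variable.

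**What to change.** Rerun the binary calculation with 24-week risks and the same 18 degrees of freedom that appear to underlie d = 0.33, and state that basis for both figures. Then report one of two equivalent statements:

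- power of about 73% for 50% versus 29.8% per annum (27.3% versus 15.0% at 24 weeks); or
- 80% power if the experimental rate is at most about 28.1% per annum (about 14.1% at 24 weeks).

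Soften the closing sentence on power to match. Add a short note that unequal home sizes would lower power slightly further, giving the CV assumed. The cost is one recalculation and a few reworded sentences, with a lower stated power. Recruitment, visits and care are unaffected.
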